### Participation rate

In order to evaluate the DIT in a CRC screening population, participation and response rate are important outcome measurements. The participation rate will be calculated by dividing the number of included participants by the total number of eligible individuals who are approached. In addition, all individuals who decline to participate will be asked about the reason for their preference for a face-to-face consultation over the DIT intervention. Also age and sex of non-participants will be collected. The response rate will be calculated by dividing the number of participants who completed the DIT by the number of included participants.

### Measurements of patient experience

#### Knowledge transfer

To assess knowledge transfer, a CRC screening specific questionnaire was developed. The knowledge questionnaire of Denters et al., developed earlier to assess informed decisions in a FIT-based CRC screening pilot study, was adjusted to the current CRC screening strategy [13]. Several questions were added and irrelevant questions were removed based on the required topics stated by the Dutch National Institute for Health and Environment (RIVM) regarding screening information that is provided [14]. Items were selected to cover the following knowledge domains: CRC in general, CRC screening specific (e.g., risk of having CRC), colonoscopy and bowel preparations. In total, 16 items were formulated as statements that can be answered with ‘true’ or ‘false’. Each correct answer given by the participant will be awarded with one point, with a maximum score of 16. After participants undergo screening colonoscopy, they will be asked (using an 11-point Likert scale) if their expectations regarding colonoscopy preparations and the colonoscopy procedure were met.

The knowledge transfer questionnaire will be validated among the first 150 participants who will receive the DIT. The validation process is beyond the scope of this study; however, it will ensure that the questionnaire effectively measures the domains, and will allow us to establish a minimum score that indicates an adequate level of knowledge.

#### Anxiety

The shortened version of the Spielberger State-Trait Anxiety Inventory (STAI-6) will be used to measure a change in patients’ state of anxiety regarding colonoscopy after receiving all information via animations in the DIT [15]. Participants will be requested to fill in STAI-6 both at the beginning and upon completion of the DIT. Furthermore, specific questions will be asked to assess a change in CRC screening specific worries. A detailed description of the questionnaire can be found in Table 1.

**Table 1 Tab1:**
[figure not shown]
Questions about patient experiences regarding the DIT

#### Satisfaction

For patient satisfaction, four measures will be included in the questionnaire. “How satisfied are you with the received information”, “What is your overall rating of the DIT?”, “Would you recommend the DIT to your peers?” and “If you are referred for another screening colonoscopy, which type of consultation would you prefer? A face-to-face consultation, an eHealth tool like the DIT, counselling via phone or counselling via a video call”. Also motives of choice and points of improvement will be evaluated. To verify participants’ satisfaction, participants will not only be requested to complete the questionnaires after completing the DIT, but also after receiving colonoscopy (Fig. 3).

**Fig. 3 Fig3:**
[figure not shown]
Flowchart illustrating time points for participants. DIT, Digital Intake Tool, Q, Questionnaire. CTC, CT-colonography. If patient and/or gastroenterologist choose not to pursue for additional diagnostic testing, no further examinations will be performed﻿

### Data collection

Demographic data and patient experiences will be collected via the DIT and will be stored in the electronic data management system, Castor Electronic Data Capture. Each participant will receive a unique study number after study enrolment. This study number will be used for all study documentation. Colonoscopy data will be reported by the gastroenterologist who performed the colonoscopy. This data is stored in the national database of the Dutch screening organization, Screen-IT. By linkage to Screen-IT we will retrieve the following colonoscopy data: BBPS, caecal intubation, reason for incomplete colonoscopy, American Society of Anaesthesiologists physical status classification (ASA), Gloucester Comfort Score and re-colonoscopy due to inadequate bowel preparation or incomplete colonoscopy. In addition, colonoscopy data will be retrieved from 1000 FIT-positive participants of the CRC screening program who did not participate in the DIT-trial. This will allow us to compare the DIT intervention to face-to-face consultation at the outpatient clinic with regard to our primary outcome.

### Statistical analysis

Continuous data will be summarized using means and standard deviations, or medians and interquartile ranges in case of skewed distributions. Categorical data will be presented in relative frequencies and counts. Comparison of normally distributed continuous variables will be done with the Student t-test or Mann-Whitney U test in case of skewed distributions. Categorical outcomes will be analysed using χ2 test. Non-inferiority of our primary outcome will be evaluated by whether the lower bound of the two sided 95% confidence interval of the observed difference in adequate bowel preparation rate is above the non-inferiority margin of 0.5%.

For repeated measurements within participants, e.g. the total STAI-6 score before and after the DIT, paired tests will be used to analyse differences. Differences are considered significant in case *p* ≤ 0.05. Other secondary outcome parameters will only be obtained from study participants who underwent the DIT intervention, these results will be reported using descriptive statistics.

Statistical analysis will be performed using IBM SPSS statistics.

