**Methods:**

This is a prospective multicentre single-arm, non-randomized study with a non-inferiority design. The DIT will triage a total of 1000 participants and inform them about CRC risk, colonoscopy, sedation, and provide bowel preparation instructions. Participants identified as high-risk (i.e., red-triaged) will be contacted by phone or scheduled for an appointment at the outpatient clinic. The primary outcome measure will be adequate bowel preparation rate, defined as the proportion of participants with a Boston Bowel Preparation (BBPS) score ≥ 6. To compare our primary outcome, we will use colonoscopy data from 1000 FIT positive participants who visited the outpatient clinic for pre-colonoscopy consultation. Secondary outcomes will include participation rate, colonoscopy adherence rate, patient experience in terms of satisfaction and anxiety, knowledge transfer, number of outpatient visits that can be averted by the DIT, and cost-effectiveness of the tool. Ethical approval was obtained from the Medical Ethical Committee of the Erasmus Medical Center (MEC-2021-0098).

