### Study design

This is a prospective, multicentre cohort study with a non-inferiority design to assess the effectiveness of a pre-colonoscopy eHealth tool in participants of a FIT-based CRC screening program. Study sites are located in the Netherlands, and include an academic hospital, regional hospitals, and endoscopy centres. In this single-arm study, all enrolled participants will receive the DIT intervention instead of standard counselling at the outpatient clinic. For analyses of our primary outcome, we will compare colonoscopy data of the study participants with that of 1000 FIT positive participants who received pre-colonoscopy counselling at the outpatient clinic of endoscopy centres that did not participate in the DIT-trial (Fig. 1). Additionally, we will assess patient-related outcome measures, including anxiety levels, satisfaction and knowledge transfer among a reference cohort consisting of 100 FIT-positive participants who received pre-colonoscopy counselling at the outpatient clinic. This study was designed according to the Standard Protocol Items: Recommendations for Interventional Trials (SPIRIT) 2013 shown in Supplementary Table 1.

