### Sample size calculation

A sample size calculation was performed for demonstrating non-inferiority of the DIT versus all participants visiting the outpatient clinic with regard to the primary endpoint; adequate bowel preparation, defined as a Boston Bowel Preparation Score (BBPS) of 6 or higher. The choice of non-inferiority design was motivated by the expectation that the DIT will improve secondary outcomes regarding costs and satisfaction. According to the Dutch national CRC screening organization at least 90% of all participants in the CRC screening program must have a BBPS of at least 6. Based on earlier data, currently in 97.5% a BBPS of 6 or higher is achieved among participants of the Dutch screening program. With a clinically acceptable difference of -0.5%, corresponding to at least 89.5% of participants achieving adequate bowel preparation, the non-inferiority margin is set at -8.0%. To achieve 90% power with a one-sided Exact test at a 2.5. significance level, 738 participants are needed. Anticipating 30% loss to follow-up or withdrawal of participants, we aim to include 1000 participants.

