It is known that individuals from ethnic minority groups are difficult to reach, especially in a CRC screening setting [24, 25]. Many of the ethnic minority groups living in the Netherlands have a poor understanding of the Dutch language and lower (health) literacy. Therefore, a limitation of this study is that non-Dutch speakers are excluded. For participation in studies, patients need to be able to read and understand the patient information form in Dutch and sign for informed consent to participate in the DIT-trial. However, in case the study shows favourable results, the DIT can easily be adapted to support additional languages. Follow-up studies should still be carried out to validate the DIT among non-Dutch speakers. However, in addition to language barriers, ethnic minority groups often experience a lower socioeconomic status (SES) [24]. In this study we will be able to evaluate the DIT among participants from different socioeconomic backgrounds, low SES serving as an approach to ethnic minority groups, based on postal code. A second limitation is the recruitment process of the study. Because of the non-randomized study design, selection bias may be present. To stay in line with the current logistics and regulations of the Dutch CRC screening program, we are unfortunately unable to conduct a randomized controlled trial. Consequently, it is possible that only individuals who prefer eHealth over regular care will be included. Nevertheless, we will collect all reasons given by non-participants refraining from participation. This will help to gain more insight into the public’s attitude and preferences towards digitalization of this process.

In conclusion, in this study we will evaluate if pre-colonoscopy outpatient visits can be replaced by an eHealth tool for FIT positive participants of the Dutch CRC screening program.

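### The Student t-test is named for comparisons that would set up to 1000 DIT participants against 100 reference patients, a ratio at which its 5% error rate is not protected if the two spreads differ materially

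*Protocol article*

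**What the plan says.** The Statistical analysis section of the protocol article gives one general sentence for continuous variables: "Comparison of normally distributed continuous variables will be done with the Student t-test or Mann-Whitney U test in case of skewed distributions". The decision rule is "Differences are considered significant in case *p* ≤ 0.05". Sidedness is not stated for this rule; I take it as two-sided. The section does not mention pooling of variances and does not tie the t-test to a named outcome or pair of groups.

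The group sizes come from elsewhere in the article. The abstract says "The DIT will triage a total of 1000 participants". The Study design section adds that "patient-related outcome measures, including anxiety levels, satisfaction and knowledge transfer" will be assessed in "a reference cohort consisting of 100 FIT-positive participants who received pre-colonoscopy counselling at the outpatient clinic". The Sample size calculation section says "Anticipating 30% loss to follow-up or withdrawal of participants, we aim to include 1000 participants".

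The Statistical analysis section assigns paired tests to repeated measurements within participants, such as STAI-6 before and after the DIT. It reports the other secondary outcomes descriptively, in DIT participants only. The primary outcome is a proportion, compared with a separate set of 1000 screening participants through a confidence interval.

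**The concern.** Taken literally, Student's t-test is the pooled-variance test. When the groups are about equal in size, unequal variances hardly affect its error rate. When one group is seven to ten times the other, that protection is gone. The pooled variance is then close to the variance of the large group, while the standard error of the difference depends mainly on the small group. If the 100 reference patients vary more than the DIT participants, the standard error is too small and false differences are declared too often. If they vary less, the standard error is too large and a real difference, including one to the DIT's disadvantage, is harder to detect. The confidence interval for the mean difference is wrong in the same direction.

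Equal spread is not guaranteed by the design. The cohorts are not randomised, and the Discussion concedes that "it is possible that only individuals who prefer eHealth over regular care will be included". What is at stake is the reliability of statements that anxiety, knowledge or satisfaction do or do not differ between the DIT and a face-to-face visit.

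**Working it through.** **Inputs.** From the article: 1000 DIT participants; 100 reference patients; 30% anticipated loss, so 1000 × 0.70 = 700; nominal level 0.05. Assumed, because the article gives no SD for any scale: the ratio r = SD(reference) / SD(DIT). The DIT SD is set to 1.

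**Formulas.** With n₁ DIT participants and n₂ = 100:

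- pooled variance = [(n₁ − 1) + (n₂ − 1)r²] / (n₁ + n₂ − 2)
- SE used by the test = √[pooled variance × (1/n₁ + 1/n₂)]
- true SE = √(1/n₁ + r²/n₂)
- actual two-sided error ≈ 2Φ(−1.96 × SE used / true SE)

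**The plan's own figure.** At r = 1, both SEs are √0.011 = 0.1049 and the error is 5.0%. The stated level is reproduced when the spreads are equal.

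**Worked case, r = 1.5, 1000 against 100.** Pooled variance = (999 + 99 × 2.25)/1098 = 1.113. SE used = √(1.113 × 0.011) = 0.111. True SE = √(0.001 + 0.0225) = 0.153. The effective critical value is 1.96 × 0.722 = 1.41, so the error is about 16%. A nominal 95% interval then covers about 84%.

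**Across the assumed range** (analytic values; simulation with 200,000 draws of normal data per setting agrees to within about 0.1 percentage point):

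| r | SE used (1000 v 100) | True SE (1000 v 100) | Error, 1000 v 100 | Error, 700 v 100 |
|---|---|---|---|---|
| 0.67 | 0.102 | 0.074 | 0.7% | 0.9% |
| 0.8 | 0.103 | 0.086 | 1.9% | 2.1% |
| 0.9 | 0.104 | 0.095 | 3.3% | 3.4% |
| 1.0 | 0.105 | 0.105 | 5.0% | 5.0% |
| 1.1 | 0.106 | 0.114 | 7.0% | 6.8% |
| 1.25 | 0.108 | 0.129 | 10.2% | 9.7% |
| 1.5 | 0.111 | 0.153 | 15.7% | 14.6% |

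**Is imbalance the cause?** With 1000 against 1000, the simulated error of the same test was 5.0% to 5.1% at r = 0.5, 1.5 and 2. The distortion therefore comes from the 100-patient reference group.

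**Does Welch's test cure it?** On the same simulated data its error was 4.9% to 5.1% for every r from 0.5 to 2, at both group sizes.

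**What does Welch's test cost if the spreads are in fact equal?** Its degrees of freedom at 1000 against 100 are 0.011² / (0.001²/999 + 0.01²/99) = 119.7, so its critical value is 1.980 against 1.962 for the pooled test, a rise of 0.9%. For an illustrative difference of 0.3 SD, power is 81.0% against 81.5%.

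**The case against.** The best case against the point has four parts.

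- **The pooled version is not spelled out.** The name Student t-test is often used loosely, SPSS prints both versions, and a condensed article may leave the choice to the analysis plan. This has some force. But the test actually named is, by convention, the equal-variance one, so this concerns stated wording rather than missing detail. If the name was meant loosely, the choice stays open until both results are on the screen.
- **The 1000 against 100 test is an inference.** The article says the measures will be assessed in the reference cohort; it does not say by which test they will be compared. That is correct. Still, collecting the same measures in outpatients has little purpose without a comparison, and the descriptive, DIT-only treatment is reserved for the other secondary outcomes.
- **Nothing shows that the spreads differ.** This stands. The Discussion raises self-selection as a source of selection bias, not of unequal variance, and neither the size nor the direction of a difference can be derived.
- **Scores that are skewed go to Mann-Whitney.** This also stands. It narrows the number of scales on which the t-test would be used.

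A reader might infer that the 5% rule fails badly whenever the spreads differ at all. The figures do not support that: SDs within 10% of each other give about 3% to 7%. A reader might also infer that the Mann-Whitney provision should be dropped. Nothing in the article makes it an error for skewed scores, and replacing it would be a preference.

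**Conclusion.** The point holds as a minor, conditional one. The named test is not protected against unequal variances at 7:1 to 10:1. With 1000 against 100, the actual error at nominal 5% is about 10% to 16% if the reference SD is 1.25 to 1.5 times the DIT SD, and about 0.7% to 2% if it is 0.67 to 0.8 times. With 700 against 100 the pattern is nearly the same. These figures rest on three assumptions: that the pooled test is meant, that the DIT and reference cohorts are compared on these scores, and that the SD ratios are as assumed.

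Only the secondary patient-reported comparisons are affected. It would be wrong to extend the point to the primary outcome, the sample size or the non-inferiority margin, because none of these uses a t-test. Changing the test also does nothing about the selection bias that the authors already acknowledge.

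**What to change.** In the Statistical analysis section, add one sentence: normally distributed scores will be compared between DIT participants and the reference cohort with Welch's unequal-variance t-test, reporting the mean difference with its 95% confidence interval. Leave the Mann-Whitney provision for skewed scores and the paired tests as they are.

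The change needs no new data and no extra patients. SPSS, the software already named, prints the unequal-variance result beside the pooled one. If the spreads prove equal, the loss is about half a percentage point of power in the example above. Fixing the choice in advance also removes any selection between the two printed results.

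### The non-inferiority margin is -8.0% in the sample-size section but an unsigned 0.5% in the analysis section, so the primary conclusion depends on which is followed

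*Protocol article*

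**What the plan says.** In the protocol article, Sample size calculation builds the margin in three steps.

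- The national requirement: "at least 90% of all participants in the CRC screening program must have a BBPS of at least 6".
- The current level: "currently in 97.5% a BBPS of 6 or higher is achieved among participants of the Dutch screening program".
- A tolerance, and the margin that follows: "With a clinically acceptable difference of -0.5" per cent, "corresponding to at least 89.5% of participants achieving adequate bowel preparation, the non-inferiority margin is set at -8.0" per cent.

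The same section gives the size: "To achieve 90% power with a one-sided Exact test at a 2.5. significance level, 738 participants are needed". It then allows for attrition: "Anticipating 30% loss to follow-up or withdrawal of participants, we aim to include 1000 participants".

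Statistical analysis gives the confidence-interval rule for the primary outcome. The lower limit of the two-sided 95% interval is to be checked to see whether the "observed difference in adequate bowel preparation rate is above the non-inferiority margin of 0.5" per cent, with no minus sign. Study design and Data collection make clear that the difference is between DIT participants and 1000 FIT-positive participants counselled at an outpatient clinic.

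**The concern.** Both sections use the term non-inferiority margin, for the same endpoint, and give different values. Both are current text, and nothing in the article reconciles them.

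The 0.5% appears to have moved from one quantity to another. In the sample-size section it is a distance below an absolute standard of 90%. In the analysis section it is applied to the difference between DIT and the comparator cohort, which is expected to be near 97.5%.

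The primary claim of the trial rests on this comparison. Someone programming the analysis from one section would run a different test from someone working from the other, and the two could report opposite conclusions from the same data. Inclusion has been running since October 2021 (Patient and public involvement). If the margin is settled only after the bowel-preparation scores have been linked, the result can no longer be called prespecified.

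**Working it through.** **Inputs.** From Sample size calculation: standard 90%, tolerance 0.5%, expected rate 97.5%, stated margin -8.0%, one-sided 2.5% level, 90% power, 738 needed, 30% loss, 1000 enrolled. From Study design: 1000 comparators. From Statistical analysis: lower limit of a two-sided 95% interval, margin 0.5%. Assumed here: a true rate of 97.5% in both groups and an unpooled Wald interval, since the article names no interval method.

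**1. The derivation of the margin.** 90 - 0.5 = 89.5, and 89.5 - 97.5 = -8.0. The sample-size section is consistent with itself on this point. The ratio of the two margins is 8.0 / 0.5 = 16.

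**2. The stated sample size.** It cannot show which margin was meant, because 738 follows from neither. The two-group formula with equal true rates is n per group = (1.960 + 1.2816)² × 2 × 0.975 × 0.025 / margin².

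- Margin 0.08: 80.04, so 81 per group.
- Margin 0.005: 20,489.5, so 20,490 per group.
- One-sample exact test of 89.5% against 97.5%: 90% power is first reached at n = 95.

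**3. Probability of declaring non-inferiority.** With 1000 × 0.70 = 700 DIT participants and 1000 comparators:

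SE = √[0.975 × 0.025 × (1/700 + 1/1000)] = 0.00769; half-width of the interval = 1.96 × 0.00769 = 0.0151.

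Probability = Φ(-margin/SE - 1.96).

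| Margin applied to DIT minus comparator | Φ argument | Probability |
|---|---|---|
| -8.0 points | 8.44 | about 100% |
| -0.5 points | -1.31 | 9.5% |
| +0.5 points (as printed) | -2.61 | 0.45% |

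Simulation of the Wald interval (400,000 runs) gave 11.4% at -0.5 and 0.56% at +0.5. With 738 instead of 700, the normal approximation gives above 99.9%, 9.7% and 0.4%.

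**4. Observed DIT rate needed to pass**, with the comparator observed at 97.5%. This is the smallest count x for which x/n - 0.975 - 1.96 × √[(x/n)(1 - x/n)/n + 0.975 × 0.025/1000] exceeds the margin.

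| Margin | n = 700 | n = 738 |
|---|---|---|
| -8.0 points | 643 (91.9%) | 677 (91.7%) |
| -0.5 points | 689 (98.4%) | 726 (98.4%) |
| +0.5 points | 695 (99.3%) | 732 (99.2%) |

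**5. The case of exact equality.** If DIT is also observed at 97.5%, the lower limit is about 0 - 1.5 = -1.5 points. That is above -8.0, but below both -0.5 and +0.5.

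**The case against.** The strongest defence is that the printed +0.5% is a slip. The sentence speaks of non-inferiority and a lower bound, and the sample-size section writes both figures with a minus sign, so a lost sign is the natural explanation. This is fair, and the superiority reading should not carry the point. But with the sign restored, -0.5 against -8.0 remains, and that conflict is enough on its own.

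A second objection is that -8.0 should not be written into the analysis section as if it were beyond question. The authors call -0.5% the clinically acceptable difference, and the stated 738 does not support -8.0 either. At -8.0 points, inadequate preparation could rise from 2.5% to 10.5%. Part of this stands: -8.0 is the margin that the sample-size section states, not one that the sample size confirms, and the sponsor must own the choice. However, the only derivation in the article leads to -8.0, and a 0.5-point margin on the difference would be far out of reach with 1000 participants.

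Third, the sample-size section also names a one-sided exact test, so the interval rule is not the only reference to a primary test. That test is given no margin other than -8.0, so it adds to the conflict.

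Finally, a full protocol or SAP, not shown here, may fix one margin. That would limit the harm, but it would not make the two statements in this article agree.

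**Conclusion.** The concern holds. The decision rule for the primary endpoint contradicts the margin that the article derives for it, by a factor of 16 if a minus sign was dropped, and in direction as well if it was not. With the comparator at 97.5% and 700 DIT participants analysed, the sections disagree for every observed DIT rate from about 91.9% up to 98.4% (margin -0.5) or 99.3% (margin +0.5). The trial's own planning value of 97.5% lies inside that range.

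The exact probabilities and thresholds rest on the assumed 97.5%, the number analysed and the Wald interval. The ordering of the three rules does not depend on them. At the planning values, the reversed verdict is the same with 700, 738 or 1000 DIT participants. This must be fixed before analysis.

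**What to change.** State one signed margin, with the direction of the difference, identically in both sections, and date it before the Screen-IT outcomes are linked. On the article's own derivation, the analysis sentence would require the lower limit of the two-sided 95% interval for DIT minus comparator to lie above -8.0 percentage points. The 0.5% would then appear only in the sample-size section, as the tolerance below the 90% national minimum.

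If the sponsor intends a different margin for the difference, it should say so, justify it and recompute the sample size. For scale, -0.5 points would need about 20,490 per group for 90% power.

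Keeping -8.0 costs one sentence, by protocol amendment or in the SAP, and no extra participants. Because 738 follows from neither margin, the sample-size calculation should be checked at the same time.

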## Introduction

### Colorectal cancer screening

Colorectal cancer (CRC) is the third most commonly diagnosed cancer worldwide and the second leading cause of cancer-related mortality [1]. CRC develops from a benign precursor lesion, detection and removal of these polyps prevent CRC, making it suitable for screening by decreasing both incidence and mortality. Therefore, CRC screening is recommended in countries where follow-up and treatment is accessible [2]. Over the past years many countries have introduced organized population-based screening programs, in European countries mostly using faecal immunochemical test (FIT) as the primary screening method [3]. In case of a positive FIT, participants are referred for a face-to-face consultation at the outpatient clinic before colonoscopy is carried out. Aim of this consultation is two-fold: assess participants’ health status and inform participants about CRC risk, colonoscopy including potential complications, sedation and bowel preparation. Both are necessary to achieve a well-informed shared decision.

The increasing burden on outpatient clinics highlights the need for healthcare providers and patients to adopt a more home-based approach to healthcare. Digital health offers a feasible solution, allowing patients to receive care without the need for in-person visits. This not only reduces the burden on the outpatient clinic, but it also offers several benefits for patients as it enables them to receive care at home. In the context of CRC screening, alternatives to the face-to-face pre-colonoscopy consultation for FIT positive participants must be explored. However, it is essential to ensure that these alternatives do not negatively impact important performance indicators of the CRC screening program such as adherence to colonoscopy, bowel cleanliness, or patient experience.

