### Secondary outcomes

Secondary outcomes include participation and response rate, colonoscopy adherence and the number of outpatient visits that are avoided by DIT. The DIT will be evaluated in terms of safety: “Are participants correctly classified as low risk?”, knowledge transfer and usability of the application. Also patient experience will be assessed in terms of satisfaction and anxiety levels both before and after completion of the DIT. Lastly, cost-effectiveness will be assessed.

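### The analysis section restricts other secondary outcomes to DIT participants, which conflicts with the planned 100-patient face-to-face cohort and leaves satisfaction, knowledge and anxiety without a stated comparison

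*Protocol article*

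**What the plan says.** All references are to the protocol article.

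- **Statistical analysis** opens with general rules: t-test or Mann-Whitney for continuous variables and chi-square for categorical outcomes. It then gives the primary non-inferiority criterion. The next paragraph states: "For repeated measurements within participants, e.g. the total STAI-6 score before and after the DIT, paired tests will be used to analyse differences". It ends with the restriction: "Other secondary outcome parameters will only be obtained from study participants who underwent the DIT intervention, these results will be reported using descriptive statistics". The 100-patient cohort is not mentioned anywhere in the section.
- **Study design** states: "we will assess patient-related outcome measures, including anxiety levels, satisfaction and knowledge transfer among a reference cohort consisting of 100 FIT-positive participants". These are people who had their counselling at the outpatient clinic.
- **Sample size calculation** says that the choice of a non-inferiority design was "motivated by the expectation that the DIT will improve secondary outcomes regarding costs and satisfaction".
- **Introduction (Colorectal cancer screening)** calls it essential that alternatives to the visit "do not negatively impact important performance indicators of the CRC screening program such as adherence to colonoscopy". The same sentence goes on to name bowel cleanliness and patient experience.
- **Data collection** ties the separate group of 1000 to the primary endpoint: "This will allow us to compare the DIT intervention to face-to-face consultation at the outpatient clinic with regard to our primary outcome".
- **Secondary outcomes** lists adherence without naming a comparator: "Secondary outcomes include participation and response rate, colonoscopy adherence and the number of outpatient visits that are avoided by DIT".

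**The concern.** One section sets up a reference cohort for three patient-reported outcomes. The section that governs the analysis says that secondary outcomes beyond the paired measures come from DIT users alone and are only described. An analyst who follows the second statement would not use the 100 patients.

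The consequence goes beyond tidiness. A non-inferiority design accepts a possible small loss on the primary outcome because something else is expected to improve. Here that is costs and satisfaction. An improvement is relative to the face-to-face visit, so a satisfaction score in DIT users alone cannot show one. Likewise, a fall or rise in STAI-6 across the DIT describes what happens around the tool. It does not say whether people end up more or less anxious than after a visit.

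The Introduction also reports an earlier Dutch screening study in which telephone consultation lowered adherence and satisfaction while bowel preparation did not differ. By the protocol's own account, bowel preparation alone may therefore miss the harm of replacing the visit.

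**Working it through.** The plan states no sample-size, power or precision figure for these outcomes, so there is nothing of its own to reproduce. The check is a comparison of texts, followed by a short illustration of precision.

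**Step 1: outcome by outcome, Study design against Statistical analysis.**

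| Outcome | Study design | Statistical analysis, read literally |
|---|---|---|
| Knowledge transfer | Measured in the 100-patient cohort | DIT participants only, descriptive |
| Satisfaction | Measured in the 100-patient cohort | DIT participants only, descriptive |
| Anxiety (STAI-6) | Measured in the 100-patient cohort | Paired before-after test in DIT users; no between-group test named |
| Participation, response, usability, visits averted | No reference data planned | DIT participants only, descriptive |

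The first two rows conflict directly. The third is a gap: the data are planned, but the only test naming STAI-6 does not use them. The last row is consistent.

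**Step 2: what the word *other* refers to.** The sentence follows directly on the paired-test rule and the significance threshold. Its nearest contrast is therefore with within-participant repeated measures, not with outcomes measured in a reference cohort. Satisfaction and knowledge then fall under *other*.

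**Step 3: would a comparison with 100 patients be informative?**

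Inputs: 1000 DIT participants and 30% anticipated loss (Sample size calculation); 100 reference patients (Study design). Assumption: the 30% loss applies to these outcomes too, which leaves 1000 × 0.70 = 700. Some questionnaires are completed within the DIT, before colonoscopy, so the loss may be smaller; the range up to 1000 is shown. No SD or target difference is given, so results are in SD units and unadjusted.

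- Standard error = sqrt(1/n_DIT + 1/100).
- n_DIT = 700: sqrt(0.00143 + 0.01000) = 0.107 SD; half-width 1.96 × 0.107 = 0.21 SD.
- n_DIT = 1000: sqrt(0.00100 + 0.01000) = 0.105 SD; half-width 1.96 × 0.105 = 0.21 SD.
- Difference detectable with 90% power at two-sided 5%: 3.2415 × 0.107 = 0.35 SD (700), 3.2415 × 0.105 = 0.34 SD (1000).
- For a proportion near 50%: 1.96 × sqrt(0.25/100 + 0.25/700) = 0.105, or 10.5 percentage points; with 1000 it is 10.3 points.

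Precision is set almost entirely by the 100 reference patients and hardly depends on the assumed loss.

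**The case against.** **A kinder reading.** Statistical analysis does state general two-group tests. The primary outcome is binary, so the continuous tests must serve something else, possibly the patient-reported scores of the reference cohort. *Other* could then mean whatever those comparisons do not cover. This is a possible reading, and it means that the authors may well intend the comparison. But the section never names the cohort, and the later, specific sentence still restricts collection to DIT participants. The literal conflict remains.

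**The paired STAI-6 test is legitimate.** The Anxiety section states the aim as measuring change after the information in the DIT, and a paired test answers that. This stands. The point is only that it does not answer the between-group question for which reference data are planned.

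**Stronger readings that the documents do not support.**

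- *Cost-effectiveness and adherence contradict the reference cohort.* A reader might infer this, but neither was ever part of the 100-patient cohort. Costing methods and their comparator may also sit in the full protocol, which is not shown.
- *The 1000-person group cannot yield an adherence rate.* What is retrieved is described as colonoscopy data, but the people are defined as FIT-positives who visited or were counselled at the clinic. No section says they are sampled at colonoscopy.
- *The satisfaction items cannot be put to the reference cohort.* Two of the four items listed name the DIT, but the reference cohort's questionnaire is not shown and may be worded differently.

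**Conclusion.** The point holds in a limited form. As written, Statistical analysis conflicts with Study design on satisfaction and knowledge transfer, and it names no between-group analysis for anxiety although reference data are planned. Followed literally, it would leave the expected satisfaction gain, and the requirement that patient experience should not worsen, without a comparison.

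An unadjusted comparison with the planned cohort would have a 95% half-width of about 0.21 SD. This assumes 700 evaluable DIT participants, 100 complete reference patients and equal SDs. It can detect moderate differences but cannot exclude small ones. Because participants choose the DIT, as the Discussion acknowledges, selection may distort any difference, and adjustment will reduce this only in part.

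The documents do not show that adherence or cost-effectiveness is contradicted. For adherence, what can be claimed depends on how the 1000 are identified, which the article leaves open.

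**What to change.** Replace the last sentence on secondary outcomes under Statistical analysis with text to this effect:

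> Knowledge score, satisfaction (items asked in both cohorts) and STAI-6 after the information has been given will be compared between DIT participants and the 100-patient reference cohort. Results are differences with 95% confidence intervals, adjusted for baseline characteristics collected in both cohorts because the comparison is not randomised. The before-after STAI-6 change will be reported as a within-DIT description. Outcomes without reference data (participation, response, usability, visits averted) will be described in DIT participants only.

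For adherence, add one conditional statement. If the 1000 are identified at the clinic visit, report the difference with its 95% interval, using the same denominator rule in both groups. If not, label adherence descriptive and make no claim that it is preserved relative to face-to-face care.

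Items already in use for DIT participants should not be reworded: inclusion has run since October 2021, and a change now would split the instrument. Restrict the satisfaction comparison to items that can be asked in both cohorts.

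The cost is a wording change and slight extra analysis on data already planned. The limitation is the modest precision that 100 patients allow, which should be stated with the results.
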